Table 1 contains all variables to be collected for the study, along with the form of the variable, its source, time point for collection and whether or not it comes from a standardised tool. Of note, the informaticist performs rigorous data validation on each queried variable. If continuous variables are found to exhibit non-linearity, they will be categorised in accordance with their distribution.

**Table 1 BMJOPEN2016011570TB1:** Characteristics of all variables used in this study

Type	Variable name	Form	Source	Time	Use of standardised tool
Explanatory	Preoperative falls	0, 1, 2, 3+	Survey	BL	Yes^21^
	Charlson Comorbidity Index	Ordinal, 0–12	CPAP H&P	BL	Yes^29^
	ASA physical status	Ordinal, 1–6	Anaesthesia record	Surgery	Yes^30^
	Procedural cardiac risk	Ordinal, 5 categories from high to low	CPAP clinician	BL	Yes^31^
Outcome	Postoperative falls	Binary (V.2); 0, 1, 2, 3+ (V.3)	Survey	30 days, 1 year	Yes^21^
	Functional dependence	Ordinal, 0–100 by 5	Survey	30 days, 1 year	Yes^32^
	Physical quality of life	Continuous, 0–100	Survey	30 days, 1 year	Yes^33^ ^34^
	Mental quality of life	Continuous, 0–100	Survey	30 days, 1 year	Yes^33^ ^34^
	In-hospital complications	Dichotomous	Survey	30 days	No
	Readmission	Dichotomous	Survey	30 days	No
Demographic	Age	Continuous	Medical record	BL	NA
	Sex	Dichotomous	Medical record	BL	NA
	Race	Nominal	Medical record (patient report)	BL	NA
	Ethnicity	Hispanic/Latino or not	Medical record (patient report)	BL	NA
	Body mass index	Continuous	CPAP nurse	BL	Yes
Confounder	Functional dependence	Ordinal, 0–100 by 5	CPAP nurse	BL	Yes^32^
	Physical quality of life	Continuous, 0–100	Survey	BL	Yes^33^ ^34^
	Mental quality of life	Continuous, 0–100	Survey	BL	Yes^33^ ^34^
	Smoking status	Current, past, never	CPAP physician or nurse	BL	NA
	Physical activity level	<4, 4–6, 6–10, >10 (METs)	CPAP physician	BL	Yes^35^
	Incontinence	Dichotomous (any issue)	CPAP nurse	BL	Yes^32^
	Toileting difficulty	Dichotomous (any issue)	CPAP nurse	BL	Yes^32^
	Mobility issue	Dichotomous (any issue)	CPAP nurse	BL	Yes^32^
	Neurological impairment (stroke, paraplegia or quadriplegia, Parkinson disease or multiple sclerosis)	Dichotomous	CPAP H&P	BL	No
	Chronic pain	Dichotomous	CPAP physician ROS	BL	No
	Dizziness/vertigo	Dichotomous	CPAP physician ROS	BL	No
	Depression	Dichotomous	CPAP H&P	BL	No
	Anxiety	Dichotomous	CPAP H&P	BL	No
Descriptive	Fall-related injury	Check all that apply	Survey	BL, 30 days, 1 year	No

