## Statistical considerations

### Sample size calculations

The required sample size is calculated based on the primary outcome, which is a fall within 30 days of surgery. Appropriate logistic regression models contain at least 10 ‘events’ per predictor variable.^20^ Since our prespecified model for postoperative falls includes 13 dependent variables (see the Analysis section), a sample with at least 130 events is required. In our population, preliminary work shows that ∼10% of patients report falling in the month following surgery. Thus, the minimum sample size needed for this study is 1300 patients.

Currently, our database contains over 9000 complete records (ie, baseline and 30-day survey) after the 16 January 2014 start date. To meet statistical assumptions of independent observations, we estimate that ∼600 records from patients with at least one previous entry in the data set will be excluded. We estimate that an additional 600 records will be excluded due to inappropriate time intervals (baseline survey to surgery <0 or >59 days; surgery to 30-day survey <20 or >120 days; or surgery to 1-year survey <275 or >455 days). Thus, our final sample size will be ∼7800.

Within this final sample, two versions of the 30-day (V.2 and V.3) and 1-year surveys (V.1 and V.2) were administered. Only V.3 of the 30-day survey and V.2 of the 1-year survey contain a validated falls question, as recommended by the Prevention of Falls Network Europe consensus group.^21^ The difference in question phrasing caused statistically significant differences in the percentage of patients reporting postoperative falls (5.5% vs 10% at 30 days and 18% vs 28% at 1-year, p<0.001). Out of the available records, about 20% (1500) completed V.3 of the 30-day survey, which is more than the 1300 required for the primary outcome. Thus, to maximise outcome validity, only these versions will be used for postoperative falls. In contrast, the readmission question contained only minor differences (‘Were you readmitted to the hospital?’ for V.2 vs ‘Check all that apply […] admitted to a hospital’ for V.3). The percentage reporting readmission was similar between surveys (5.2% vs 5.7%, p=0.416), so the results from both versions will be combined. The remaining outcomes were identical and will use all available data from both versions of the 30-day and 1-year surveys.

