Aim 2 explores whether a preoperative history of falls serves as a useful tool for predicting surgical outcomes. First, we will calculate a crude dose–response relationship between the number of falls at baseline (0, 1, 2, 3+) and each outcome (postoperative falls, postoperative functional dependence, postoperative quality of life, in-hospital complications and 30-day readmission). For comparison, we will also calculate the crude dose–response relationship for a falls and injuries composite scale.^27^ We will examine the bivariate relationship between preoperative falls and each complication subcategory (heart/stroke, lung, blood clots, kidney/intestine, nerve injury, infection, delirium or other) using χ^2^ tests for the purpose of hypothesis generation.

To assess the relationship after controlling for important confounders, we will use logistic regression (categorical outcomes) and linear regression (continuous outcomes). Specifically, we will use forced entry of all prespecified variables. We will check all models for linearity of logit, multicollinearity, influential cases, conformity to linear gradients and goodness of fit. Since the number of possible interaction terms is large (between 45 and 91 per model), including all of them creates an unacceptably large risk of type I error. Therefore, our statistical consultant ([name]) recommended selecting only 10% of the most clinically relevant interaction terms. Using a combination of prior research and clinical judgement, two investigators ([name] and [name]) selected the 10% most clinically relevant interaction terms for each model. The online supplementary material contains these prespecified interaction terms. Non-significant interaction terms (p>0.01) will be removed from the model.

10.1136/bmjopen-2016-011570.supp8Supplementary data

Each model will include the following demographic and explanatory variables: age, sex, race (white vs non-white), BMI, preoperative falls history (0, 1, 2, 3+), Charlson Comorbidity Index (≥3 vs <3), American Society of Anesthesiology (ASA) physical status (≥3 vs <3) and procedural cardiac risk. On the basis of a careful literature search of each outcome variable (see the Literature search and review section), we selected confounding variables that are both routinely collected and known at the time of surgery planning. Outcome variables and their corresponding outcome-specific confounders are listed below.

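### Charlson index and ASA class are collected as graded scores but enter every model only as a cut at 3, with no reason given; if risk is graded, some comorbidity confounding is left in the falls-history estimate

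*Protocol article*

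**What the plan says.** Table 1 of the protocol article lists the Charlson index as ordinal from 0 to 12 and ASA physical status as ordinal from 1 to 6. The Analysis section then fixes their form: "Charlson Comorbidity Index (≥3 vs <3), American Society of Anesthesiology (ASA) physical status (≥3 vs <3"). The scope is general: "Each model will include the following demographic and explanatory variables". Neither the Analysis nor the Limitations section explains the cut or mentions what it loses.

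Three other statements bear on it:

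- The purpose of the models: "To assess the relationship after controlling for important confounders, we will use logistic regression (categorical outcomes) and linear regression (continuous outcomes").
- The rule on categorising, in the text before Table 1: "If continuous variables are found to exhibit non-linearity, they will be categorised in accordance with their distribution".
- The model checks: "We will check all models for linearity of logit, multicollinearity, influential cases, conformity to linear gradients and goodness of fit".

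The sample size for the primary model rests on a count of predictors: "Appropriate logistic regression models contain at least 10 ‘events’ per predictor variable", and "Since our prespecified model for postoperative falls includes 13 dependent variables (see the Analysis section), a sample with at least 130 events is required" (predictors are evidently meant).

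**The concern.** Comorbidity is an obvious alternative explanation for a link between earlier falls and poor surgical outcome. Cutting at 3 treats a Charlson score of 0 like a 2, and a 3 like a 10; ASA 1 is treated like ASA 2. If sicker patients within each half fall more often before surgery and also do worse afterwards, the binary terms cannot remove that difference. The falls-history term picks up the rest, in the direction of the study hypothesis.

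The models differ in how exposed they are. The models for falls, function and quality of life also carry variables such as mobility, activity level or a baseline score, which may absorb part of the difference. The complications model adds only smoking to the eight common variables. Apart from age, BMI and procedural cardiac risk, its control for comorbidity rests on the two binary terms.

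The plan checks linearity elsewhere and reserves categorising of continuous variables for cases where linearity fails. For these two scores the gradient is removed before it can be examined.

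**Working it through.** **1. The plan's own count.** Eight common variables (age, sex, race, BMI, falls history, Charlson, ASA, procedural cardiac risk) plus five for postoperative falls make 13. Then 13 × 10 = 130 events. The Sample size section states that "preliminary work shows that ∼10% of patients report falling in the month following surgery", so 130 / 0.10 = 1300 patients. The stated figure reproduces exactly.

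**2. The same count with scores.** One linear term for Charlson and one for ASA use 1 + 1 degrees of freedom, as the two binary terms do. The count stays at 13, 130 and 1300. With about 1500 patients there are 1500 × 0.10 = 150 events, and 150 / 13 = 11.5 per predictor. Full categories would cost more: 11 other predictors + 12 Charlson indicators + 3 for ASA in four levels = 26, and 150 / 26 = 5.8.

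The secondary models have room: complications 0.28 × 7800 = 2184 events for 8 + 1 = 9 predictors; readmission 0.055 × 7800 = 429 events for 8 + 2 = 10.

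**3. Possible size of the bias.** From the documents: 26% preoperative fallers and a 10% outcome. Assumed, because the documents do not give them: Charlson 0/1/2 in 40/20/15% and 3 or more in 25%; ASA 1 to 4 in 8/47/39/6%; latent correlation 0.6; the same comorbidity effects on falls history and on outcome. The true falls odds ratio was set to 1.0, with 1,000,000 simulated patients per scenario. With graded (log-linear) effects the estimated falls odds ratio is:

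| Assumed OR per Charlson point / ASA class | Unadjusted | Cut at 3 | Linear scores |
|---|---|---|---|
| 1.10 / 1.2 | 1.09 | 1.02 | 1.00 |
| 1.15 / 1.4 | 1.26 | 1.06 | 0.99 |
| 1.25 / 1.6 | 1.73 | 1.18 | 1.01 |
| 1.35 / 1.8 | 2.38 | 1.30 | 1.00 |

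The cut removes most of the excess: in the third row (1.733 − 1.176) / (1.733 − 1) = 76%.

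**4. Other shapes of the Charlson effect (ASA still graded).**

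- Step at 3: the cut leaves 1.003 to 1.048; linear scores leave 1.006 to 1.105.
- Rise to 3, then plateau: the cut leaves 1.013 to 1.110; linear scores leave 1.007 to 1.086.

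**5. Complications setting.** With a 28% outcome, n = 7800, Charlson mean 1 to 2, score correlation 0.5, graded effects and the planned α = 0.01:

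| Assumed OR per point / class | Falls OR with the cut | False-positive rate |
|---|---|---|
| 1.10 / 1.2 | 1.01–1.02 | 1.2–1.4% |
| 1.15 / 1.4 | 1.03–1.07 | 2–7% |
| 1.25 / 1.6 | 1.08–1.17 | 10–49% |

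Linear scores give 0.99 to 1.01 throughout. A hand check of one entry: the standard error of the log odds ratio is about 1 / √(7800 × 0.26 × 0.74 × 0.28 × 0.72) = 0.0575. Then ln(1.08) / 0.0575 = 1.34, and the chance of exceeding 2.576 is about 11%, in line with the simulated 10%.

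A separate run in this setting gave 0.99–1.03 with the cut against 0.99–1.05 with linear scores under a step at 3, and at most 1.05 with the cut under a plateau.

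**The case against.** The size rests wholly on assumed inputs. The documents give no Charlson or ASA distribution, no correlation between them and no effect sizes. Where the truth is log-linear, the linear fit is correct by construction, so its near-perfect result is no surprise. Under a step or a plateau the two codings perform about equally. With weak effects the bias is negligible, and in every graded scenario of the first table the cut already removes roughly three quarters or more of the crude excess. All of this stands.

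The simulated models are also simpler than the planned ones: falls history is binary rather than 0, 1, 2, 3+, and the other covariates are absent. In a check with three correlated covariates, absorption was small (1.12 to 1.11), so this point carries less weight. An odds ratio does not describe the quality-of-life models, which use linear regression with the baseline score; no figure is offered for them.

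A finer score is no complete cure. The Limitations section says that the completeness of the Charlson source is unknown; with 30% of points missed, linear fits still left up to 1.07.

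A reader might infer three stronger things. None is supported:

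- That the cut was made to save degrees of freedom. The protocol gives no reason. The cut saves none against a linear term, but it does against full categories.
- That the plan breaks its own rule on categorising. That rule is written for continuous variables, and these are ordinal scores.
- That every falls-history estimate is confounded by a known amount. This depends on a risk shape that the documents do not give.

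**Conclusion.** The point holds as an unexplained loss of collected confounder information in all models. Residual comorbidity confounding towards the hypothesis is expected if risk is graded across the scores and comorbidity raises both preoperative falls and the outcome. It is not established for every estimate.

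Under assumed graded effects the spurious odds ratio is about 1.01 to 1.2, and 1.3 under the strongest effects tried. For scale, the protocol's minimum important difference is 20%. Its detectable increases are 58% for postoperative falls, 34% for readmission, 15% for functional decline and 12% for complications. The bias therefore matters most for the large-sample secondary outcomes, above all complications, where even a small bias can raise the false-positive rate above the planned 1%. Against the 58% detectable for the primary outcome it is small in most scenarios. This is an avoidable weakness of uncertain size, worth changing because the change is cheap. It does not invalidate the plan.

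**What to change.** In the Analysis section, enter the Charlson index as a score (upper tail truncated if sparse) and ASA class as an ordinal trend term in each model. State that the linearity check already planned applies to both, and that a few categories or a spline will replace the linear term if it fails. Keep the cuts at 3 for descriptive tables or as a sensitivity analysis. If the cuts are kept as the main form, give the reason and add the possible residual confounding to the Limitations section.

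Cost: a change of wording. The scores are already collected, and by the plan analysis starts only after the protocol is accepted. With linear terms the 13-predictor, 130-event and 1300-patient figures stand; categories or a spline would use more degrees of freedom, which matters mainly for the primary model at about 150 events. The two covariate odds ratios become per point and per class rather than high versus low, and a linear term assumes equal steps unless the check says otherwise.

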## Specific aims

*Aim 1*: Describe characteristics of postoperative falls in an unselected surgical population, including their rate, timing, associated injuries and risk factors.

We hypothesise that the occurrence, injuries and risk factors of postoperative falls will be similar to those of preoperative falls, and the rate of postoperative falls will decline from 30-days after surgery to 1 year after surgery.

*Aim 2a*: Determine whether a preoperative history of falls serves as a useful tool for predicting falls in the 30 days (primary outcome) and 1 year following surgery of all types.

*Aim 2b*: Determine whether a preoperative history of falls predicts patient-centred outcomes including functionality and quality of life at 30 days and 1 year after surgery (secondary outcomes).

*Aim 2c*: Replicate findings that a preoperative history of falls predicts in-hospital surgical complications and readmission at 30 days (secondary outcomes).

We hypothesise that a history of preoperative falls will predict poor postsurgical outcomes, including postoperative falls, functional dependence, poor quality of life, in-hospital complications and readmission.

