## Study design

A substudy of SATISFY-SOS, this prospective cohort study will synthesise three sources of information:
Preoperative ‘baseline’ survey—completed by patient at the preoperative assessment clinic within 4 weeks of surgery.Postoperative ‘30-day’ and ‘1-year’ surveys—completed by patients ∼30 days and 1 year following surgery, respectively.Electronic medical record—provides additional demographic and medical data.

The surveys were developed following a consultative process, including people with relevant expertise. The guiding principle was to formulate a survey that would be meaningful, reliable and practical for widespread dissemination to an unselected patient population. All surveys are available in the online supplementary material.

10.1136/bmjopen-2016-011570.supp2Supplementary data

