Presence or absence of at least one fall in the 30 days (primary outcome) and 1 year following surgery:
Physical activity level (<4 vs >4 metabolic equivalents (METs));Baseline altered elimination (bowel or bladder);Baseline mobility abnormality;Dizziness/vertigo;Depression.▸Barthel Index that is worse than baseline, at 30 days and 1 year after surgery:
Baseline Barthel Index score;Neurological impairment;Mood disorder (depression or anxiety);Smoking status.▸Physical quality of life score, at 30 days and 1 year after surgery:
Baseline physical quality of life score;Preoperative physical activity level (<4 vs >4 METs);Chronic pain;Mood disorder (depression or anxiety);Smoking status.▸Mental quality of life score, at 30 days and 1 year after surgery:
Baseline mental quality of life score;Chronic pain;Mood disorder (depression or anxiety).▸Presence or absence of any complication that occurred in the hospital, as reported in the 30-day survey:
Smoking status.▸Presence or absence of readmission at 30 days, as reported in the 30-day survey:
In-hospital complications (30-day survey);Incontinence.

After running each model, we will substitute the number of falls (0, 1, 2, 3+) explanatory variable for the falls and fall injuries composite scale^27^ to evaluate which scale better predicts outcomes. Since we test multiple hypotheses, the threshold for significance will be α=0.01. We will report results using ORs and 99% CIs, along with variance estimates for regression parameters.

Using SAS/STAT software, V.9.4 (SAS Institute, Cary, North Carolina, USA), [name] will perform all analyses. Analysis will begin only after acceptance of this protocol for publication. This approach reassures readers that key analyses were truly prespecified rather than post hoc. If the authors decide to perform post hoc analyses, these will be described as such and will be performed for the purpose of further hypothesis generation.

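### The adjusted functional outcome counts any Barthel drop from a nurse-sourced baseline to a patient survey, so a difference between sources can create or hide events, and it models decline although the aims name dependence.

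*Protocol article*

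**What the plan says.** All references are to the protocol article.

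- **Outcome in the adjusted model (Analysis).** The functional outcome is "Barthel Index that is worse than baseline, at 30 days and 1 year after surgery". No margin is given. The outcome-specific covariates are "Baseline Barthel Index score;Neurological impairment;Mood disorder (depression or anxiety);Smoking status".
- **Sources (Table 1, Data to be collected).** The baseline row reads "Functional dependence Ordinal, 0–100 by 5 CPAP nurse BL". The outcome row reads "Ordinal, 0–100 by 5 Survey 30 days, 1 year". Study design says that the follow-up surveys are "completed by patients ∼30 days and 1 year following surgery, respectively".
- **Aims.** The hypothesis in Specific aims concerns poor outcomes "including postoperative falls, functional dependence, poor quality of life, in-hospital complications and readmission". It names dependence, not decline.
- **Crude analysis (Analysis).** A dose–response analysis by number of preoperative falls is planned for "each outcome (postoperative falls, postoperative functional dependence, postoperative quality of life, in-hospital complications and 30-day readmission".
- **Power (Sample size calculations).** The assumptions are a 20% rate of functional decline, 26% of patients exposed, two-sided α of 0.05 and 7800 patients. These are said to give 80% power for a 15% increase in decline.
- **Limitations.** On functional dependence, the text says only that the question is the same in both survey versions. It does not mention that baseline and follow-up come from different sources.

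**The concern.** The event is the sign of a difference between two scores, and the two scores come from different sources. With steps of 5 and no margin, a one-step disagreement on a single item is enough to change a patient's status. If the survey reads lower than the nurse's record, a stable patient becomes an event. If it reads higher, a true decline is hidden. A patient recorded at 100 can only stay level or worsen, so for that patient a lower survey reading can only add an event. Having the baseline Barthel score in the model does not remove this, because the error is already in the event.

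Error that is equal in both fall-history groups dilutes a real association. Error that depends on fall history can produce a false one.

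The second issue is what the model tests. Aims and Table 1 present functional dependence on a 0–100 ordinal scale, but the adjusted model tests decline. A patient at 60 before and after surgery is dependent throughout and counts as event-free. The quality-of-life outcomes in the same list are handled differently: the follow-up score is modelled with the baseline score as covariate.

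**Working it through.** **Inputs from the protocol (Sample size calculations).** N = 7800; 26% exposed, so 0.26 × 7800 = 2028 fallers and 5772 non-fallers; decline 20%; a 15% relative increase, so 0.20 × 1.15 = 0.23; two-sided α = 0.05.

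**Step 1: the plan's own figure.** A two-proportion test with pooled variance, 20% versus 23%, 5772 versus 2028 patients, has power 81.1%. The increase detectable with 80% power is 14.8% if 20% is the rate in non-fallers, and 15.1% if it is the overall rate. The stated 15% reproduces, so there is no arithmetic error.

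**Step 2: equal false drops (assumption).** Let f be the share of truly stable patients whose score falls at least one step only because the source changed, equal in both groups, with every true decline still detected. Observed rate = p + (1 − p) × f. For f = 10%: 0.20 + 0.80 × 0.10 = 0.280 and 0.23 + 0.77 × 0.10 = 0.307.

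| f | Non-fallers | Fallers | Relative increase | False share of non-fallers' events | Power, α = 0.05 | Power, α = 0.01 |
|---|---|---|---|---|---|---|
| 0 | 20.0% | 23.0% | 15.0% | 0% | 81% | 61% |
| 5% | 24.0% | 26.9% | 11.9% | 17% | 72% | 49% |
| 10% | 28.0% | 30.7% | 9.6% | 29% | 64% | 40% |
| 15% | 32.0% | 34.6% | 8.0% | 38% | 56% | 32% |

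The last column uses the significance threshold set in the Analysis section. The fall from 81% to 61% in its first row comes from the stricter α alone, not from the source change.

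**Step 3: false drops that depend on fall history (assumption).** No true difference, 20% decline in both groups, false drops of 5% in non-fallers and 10% in fallers:
- non-fallers: 0.20 + 0.80 × 0.05 = 0.24
- fallers: 0.20 + 0.80 × 0.10 = 0.28
- odds ratio: (0.28/0.72) / (0.24/0.76) = 1.23

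This exceeds the 20% that the protocol sets as its minimum important difference for proportions or odds ratios.

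**Step 4: what an ordinal model recovers.** Take the hardest case: every baseline is 100, false drops are exactly one step, and true decliners are spread over 95, 90 and 85 or lower, with 20% to 50% of them at 95 (all assumptions).
- Equal error of 10%: power 67% to 70%, against 64% for any drop.
- Equal error of 15%: power 62% to 65%, against 56%.
- The Step 3 scenario: false odds ratio 1.18 to 1.20, against 1.23.

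The gain is real but modest. With a baseline of 100, any drop and a follow-up score below 100 are the same event, so the ordinal model still contains that cut-point.

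**The case against.** The strongest reply has four parts.

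- **The source label is thin evidence.** Table 1 names the nurse as the source but does not say whether the nurse observed function or wrote down the patient's answers. In the second case both scores rest on self-report and the contrast is much weaker. The same standardised tool is cited at both times. This stands: a reader might infer that a change of rater is itself an event, but only a recorded drop is, and the documents do not show how often one would arise this way.
- **The error rates are assumed, and in one direction.** The scenarios only add events. A survey score above the nurse's would hide declines instead. This stands, and the net direction of bias is unknown.
- **Decline is a coherent outcome.** The power statement uses it, and counting 60 to 60 as event-free is right for a question about worsening. A reader might infer that dependence is not analysed at all, but the crude dose–response analysis lists it. That label may refer to the same decline variable; the text does not settle this. What remains is that the adjusted model tests something other than the outcome named in the aims and Table 1.
- **The remedy does not cure the problem.** Step 4 confirms this. The case for it rests on using the full scale, matching the stated aim and agreeing with the quality-of-life models, with only a partial gain in robustness.

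**Conclusion.** The concern holds in a limited form. The protocol fixes an adjusted outcome that any one-step drop satisfies, across two different sources, without a margin and without acknowledging the change of source. It also names one outcome in the aims and models another. Both points can be read directly from the text.

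The size is conditional. Under assumed equal false drops of 5% to 15%, crude power falls from 81% to between 72% and 56%. Under assumed false drops of 10% versus 5% by fall history, an odds ratio of 1.23 appears with no true effect. The documents contain no disagreement rate, so these figures show sensitivity and are not estimates of actual bias. The stated power calculation is arithmetically sound. The outcome is secondary, and the primary outcome, falls within 30 days, is not affected. The change is worth making because it needs no new data and the protocol says that analysis has not begun.

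**What to change.** 1. Make the follow-up Barthel score the adjusted functional outcome, analysed by ordinal (proportional-odds) regression, with the baseline Barthel score, already a covariate, kept in the model. This matches the aims, Table 1 and the quality-of-life models.
2. Keep worse than baseline as a supporting analysis, and add a sensitivity analysis that requires a drop of more than one 5-point step. If the association weakens clearly under the larger drop, one-step differences between sources may be driving it.
3. State in the Limitations that the baseline score comes from the clinic nurse and the follow-up score from the patient's survey, and say how the nurse obtained it.
4. Use one name for the outcome in the aims, Table 1, the power statement and the crude and adjusted analyses.

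The cost is one changed outcome definition and model line, one extra analysis and a few sentences. A common odds ratio is less simple to report than a per cent who declined. The larger-drop analysis has fewer events. The ordinal model recovers only part of the loss from random one-step error and does not remove error that depends on fall history.
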